### Data Collection

The enrollment survey, which will collect baseline health and sociodemographic data about the child, caregiver, and household, will be administered by CIs using a mobile phone equipped with Open Data Kit software. Specifically, we will collect information on the caregiver’s phone ownership and usage and the caregiver’s demographics including age, education, marital status, and literacy level, household assets, number and type of livestock owned, water source, type of cooking fuel used, and current occupation. When children reach 12 months of age, a CI will conduct a household visit to document measles immunization status. Caregivers will be asked to present their maternal and child health (MCH) booklet so that CIs can record a written immunization history of Bacillus Calmette–Guérin, pentavalent, polio, and measles vaccines. If the MCH booklet is unavailable, CIs will collect a verbal report of the child’s immunizations. If the child is found to not be up to date with all vaccinations, the CI will refer the caregiver and infant to the nearest clinic, but the study will not pay for transport or health care costs. In addition to the immunization history, the follow-up survey will ask questions surrounding text message reminders and incentives, as applicable. Costs of the interventions (eg, SMS, mobile-money incentive and staff time) will be collected throughout the study for future cost-effective analyses.

Data will be stored in a secure database at KEMRI Center for Global Health Research (KEMRI/CGHR) in Kisian, Kenya. Photo identification and key cards are required to enter the data storage area. Only a limited number of authorized staff will have access to the data. Data will be deidentified for analysis and will only be shared with investigators of the study protocol. Caregivers will be assigned a study ID number in line with current HDSS operating procedures. Linkages with HDSS data will be made so that the CHW enrollment approach can be compared with existing HDSS population estimates.

### Outcomes

The primary outcome is the proportion of children who received measles vaccination by 10 months of age. Measles vaccination at 12 months is a secondary outcome. Data for primary and secondary immunization outcomes will come from written immunization records found on the child’s MCH booklet at household follow-up visits. If dates in MCH booklet are illegible, missing, or vaccination history was provided verbally, the health facility immunization registries will be searched to identify vaccines given. Data from our previous study conducted in the same setting indicated that over 95% of caregivers had an MCH booklet at 12 months of age [15].

### Data Analysis

The analysis and reporting of results will be conducted in accordance with the Consolidated Standards of Reporting Trials [22]. A blinded statistician will conduct analyses for primary and secondary outcomes. The primary analyses will be conducted with intention-to-treat principles. The primary outcome, measles immunization at 10 months of age, will be defined as a binary variable. Log-binomial regressions to calculate risk ratios for achieving the primary outcome will be calculated for the intervention arms as compared with the control arm. As a secondary analysis of the primary outcome, time-to-immunization curves will be constructed using the Kaplan-Meier method, and study arms will be compared using the Cox model. The 25th, 50th, and 75th percentiles for time to measles immunization will also be calculated by the study arm. Effect estimates will be presented in whole and stratified on mobile phone ownership and clinic proximity. Mobile phone ownership will be defined as a binary variable (*owns a mobile phone* or *doesn’t own a mobile phone*). Additional stratified estimates will be presented based on calculated risk factors for not receiving measles vaccine in control arm infants. Adjusted analyses will be conducted if our randomization produced imbalanced sociodemographic characteristics by the study arm. A per-protocol analysis of primary and secondary outcomes will also be conducted. Per-protocol delivery of the interventions will be defined as caregivers who were sent 2 text message reminders for measles vaccination in the 2 intervention arms and as caregivers who were sent an incentive in the third study arm.

Socioeconomic quintile scores will be calculated using a multiple correspondence analysis of household assets, livestock owned, water source, type of cooking fuel used, and occupation [23]. In villages where HDSS and CHWs are active, we will conduct a sensitivity and specificity analysis of our CHW approach to identify age-eligible children. The HDSS database, which relies on village reporters to enumerate the population, will be used as the gold standard. We will compare the costs of a CHW versus HDSS approach of identifying eligible children. An alpha of .05 will be assumed for all statistical tests of significance.

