### Sample Size

The primary objective is to assess the effect of the interventions on their ability to improve measles vaccination coverage by an absolute difference of 15 percentage points at 10 months of age as compared with the control arm (eg, 70% measles coverage in the control arm and 85% coverage in an intervention arm). This effect size was selected because it represents a meaningful public health impact and could motivate decision makers to adopt this intervention. Data for the sample size calculation come from the M-SIMU trial; where we found a measles vaccination coverage of 70% at 10 months of age in control arm children [15]. Assuming a 70% outcome in the control group, an absolute 15% difference in the primary outcome between control and intervention arms, a type 1 error (alpha) of .05 and a power (1-beta) of 0.80, we calculated that 134 caregivers are needed in each study arm. Adjusting our sample size for a 25% loss to follow-up (death, outmigration, verbal report of measles vaccination at 10 months of age, and other reasons), our adjusted sample size is 179 participants per study arm, yielding a total sample size of 537 caregivers across the 3 study arms.

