### Limitations

This study has several potential limitations. First, not all caregivers will provide written immunization records at the 12-month follow-up visit. Evidence from other settings implies that they may under or overestimate actual vaccination coverage [24-26]. It is likely that social desirability bias may lead those who received an incentive in this study to verbally report vaccination. At the same time, this bias may be minimal as the M-SIMU trial found that over 95% of caregivers had an MCH booklet at 12 months of age [15]. An additional limitation of this study is that the CIs who will collect measles vaccination status at the follow-up visit will also be responsible for assigning the study arm at enrollment (ie, not blinded to study arm allocation). To minimize the risk of outcome ascertainment bias, the follow-up questionnaire will be structured to collect vaccination data before any questions that identified the study arm allocation. For CIs to be biased when ascertaining vaccination status, they would have had to rely on their memory of the participant’s study arm allocation during the enrollment visit, which was conducted 4 to 6 months before the follow-up visit.

We hypothesize that the interventions will improve measles vaccination coverage and that they will be effective in many of the traditionally hard-to-reach populations. By designing this study with scalability in mind, the results of this trial will hopefully approximate the effects of national or subnational programs.

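### The extra risk strata are, on the natural reading, chosen from this trial's control outcomes and compared with those same controls, biasing the high-risk estimate upward

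*Protocol article*

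**What the plan says.** The protocol article's Data Analysis section sets out log-binomial models in which "risk ratios for achieving the primary outcome will be calculated for the intervention arms as compared with the control arm". It then names two stratifiers in advance: "Effect estimates will be presented in whole and stratified on mobile phone ownership and clinic proximity". A further set follows: "Additional stratified estimates will be presented based on calculated risk factors for not receiving measles vaccine in control arm infants".

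For this further set the section gives no list of factors, no selection rule, no outside data source, and no separation between the control children who choose the factors and those who are compared. The same section sets alpha at .05 for every significance test. It presents these estimates as additional to the main ones but does not call them exploratory.

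The likely candidates are the baseline items in Data Collection: "age, education, marital status, and literacy level, household assets, number and type of livestock owned, water source, type of cooking fuel used, and current occupation".

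**The concern.** A factor qualifies as a risk factor because control children who carry it were vaccinated less often. Part of that deficit is real and part is chance. When the same control children become the comparator, the chance part stays in the high-risk stratum as low control coverage, and a matching surplus sits in the low-risk stratum. The factors were not chosen on intervention-arm outcomes, so coverage there has no such distortion. The intervention therefore tends to look better in high-risk children and worse in low-risk children, with no effect modification at all.

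At stake is the reading of a subgroup result. A clear gap between the strata could lead a programme to target certain families when the gap comes from how the strata were picked.

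**Working it through.** **Inputs.**
- Control coverage at 10 months, from Sample Size: "where we found a measles vaccination coverage of 70% at 10 months of age in control arm children".
- Design effect, from Sample Size: "70% measles coverage in the control arm and 85% coverage in an intervention arm".
- Error rates, from Sample Size: "a type 1 error (alpha) of .05 and a power (1-beta) of 0.80".
- Children per arm: 134 evaluable, 179 enrolled (Sample Size).
- Assumptions, because the article is silent: 10 independent binary candidate factors (Data Collection names roughly that many items), each carried by half the children, with the factor showing the largest control-arm coverage difference selected.

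**The plan's own figure.** The article gives no figure for the stratified estimates, but the arm sizes can be checked. The two-sided formula for two proportions is n = [1.96√(2 × 0.775 × 0.225) + 0.842√(0.70 × 0.30 + 0.85 × 0.15)]² / 0.15². This gives 121, or 134 with continuity correction. Then 134 / 0.75 = 178.7, rounded up to 179, and 3 × 179 = 537. The stated sizes reproduce.

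**Closed-form check, all factors noise, no treatment effect.**
1. Each factor splits 134 controls into about 67 and 67. The standard error of the coverage difference is √[0.70 × 0.30 × (1/67 + 1/67)] = 0.079.
2. The mean of the largest absolute value among 10 independent standard normals is 1.88, so the selected factor shows an expected difference of 1.88 × 0.079 = 0.149.
3. Overall control coverage stays at 70%, so half the difference falls on each side: 0.149 / 2, or about 7.5 points. High-risk controls sit near 62.5% and low-risk controls near 77.5%. The intervention arm is at 70% in both.
4. On the protocol's scale the risk ratios are 70 / 62.5 = 1.12 and 70 / 77.5 = 0.90, where the truth is 1.00.
5. With 179 per arm the standard error is √(0.21 × 4 / 179) = 0.0685, and the bias is 1.88 × 0.0685 / 2, or about 6.4 points.

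**Simulation, same selection rule, no true effect, 10 candidates.**

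| Candidate factors | Per arm | Bias, high-risk stratum | Rejection at .05 |
|---|---|---|---|
| All noise | 134 | +7.5 points | 12.6% |
| Three real, log odds ratio 0.7 | 134 | +5.0 | 7.4% |
| One real, log odds ratio 1.0 | 134 | +3.1 | 6.7% |
| Three real, log odds ratio 0.7 | 179 | +3.9 | 6.1% |
| One real, log odds ratio 1.0 | 179 | +1.7 | 6.0% |

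The low-risk stratum shows the mirror image. Repeat runs agree to within a few tenths of a point and about one percentage point of rejection.

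**With a true 15-point effect everywhere, all factors noise.** The strata show 22.4 and 7.6 points at 134 per arm (15 ± 7.4), and 21.5 and 8.5 at 179 (15 ± 6.5). With two real factors of 10 points each among the 10, they show 21.2 and 8.9.

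**If a fitted risk score were used instead of single factors.** The top third of a logistic score from 10 factors, three of them real (log odds ratio 0.7), gives a null risk ratio of 1.22 at 134 per arm. The article speaks of risk factors, not a score, so this is a sensitivity case only.

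**Does independent derivation cure it?** Yes. When independent data choose the factors, the bias vanishes and rejection is about 5%. For the score, an outside control sample or a half-and-half split of controls gives null risk ratios of 0.99 to 1.005. False positives favouring the intervention are then 2.2% to 2.8%, against a nominal 2.5%.

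**Does an interaction test cure it?** No. With strata chosen from the same controls and 10 candidates, the interaction test falsely rejected in 22% to 26% of trials.

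**The case against.** The strongest reply has four parts.

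- **These estimates are secondary.** That stands. The trial's objective is the overall effect, and nothing says a conclusion will rest on these strata. It limits the seriousness but does not remove the bias.
- **A journal article leaves detail to the full protocol or analysis plan.** It does, and a missing factor list or cut-off is no fault here. But the article does state where the factors come from, and that source is the difficulty. The sentence might mean another study's controls. However, Setting and Participants, Outcomes and Sample Size each name the earlier trial when they draw on it, and this sentence does not.
- **Noise-only figures exaggerate.** That stands too. Education, household assets and similar items plausibly predict vaccination, and real predictors reduce the bias. Hence the range.
- **The earlier trial may be a poor source.** Its control-arm measles coverage appears as 51% by 12 months in Setting and Participants but 70% at 10 months in Sample Size. It also enrolled infants under 5 weeks of age by another route (Differences Between Previous Studies). Its use therefore depends on a check that its covariates match.

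Three stronger readings are tempting, and the documents support none of them. A reader might infer that a larger high-risk effect is certain. It is only expected: in null trials the high-risk estimate exceeded the low-risk one in about 61% to 97% of runs, depending on the setting, against 50% by chance. A reader might infer that the artefact confirms the trial's own hypothesis. Limitations says only that "they will be effective in many of the traditionally hard-to-reach populations", which does not predict a larger effect there than elsewhere. And a reader might extend the problem to phone ownership and clinic proximity, but those were named without looking at outcomes and do not carry this bias.

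**Conclusion.** The concern holds for the additional risk strata only. The direction of the expected bias was the same in every setting examined. Its size rests on assumptions the article does not supply: the number of candidates, the selection rule and how strongly the factors predict vaccination. With the strongest of 10 binary factors selected and 134 to 179 per arm, it is about +2 to +7.5 points in the high-risk stratum and the reverse in the low-risk one, with 6% to 13% rejection at the .05 level. The upper end is half the 15-point design effect (7.5 / 15). The primary comparison is untouched. This should be corrected before analysis, but it does not threaten the trial's main result.

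**What to change.** Choose the risk factors without using this trial's control outcomes, and freeze them before unblinding. The earlier trial's control arm in the same setting is one possible source, if its covariates match. If no outside source serves, derive the strata for control children by cross-fitting, leave-one-out prediction or sample splitting, so that no control child's outcome helps to place that child.

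Report an arm-by-stratum interaction for these derived strata, in addition to the independent derivation and not in its place. Label the analysis exploratory.

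The cost is a sentence or two in the analysis text and a little programming. The risk strata will be somewhat less precise if they are derived externally or by sample splitting.

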### Procedures

#### Enrollment

During their monthly visit, CHWs will identify households with children aged 6 to 8 months. CHWs will approach caregivers of age-eligible children, provide a brief explanation of the study, and answer any questions the caregiver might have. The CHWs will call the field supervisor to notify the study team that they have identified a child aged 6 to 8 months. The field supervisor will then assign a CI to visit the child’s compound to explain the trial and screen the caregiver for the eligibility criteria as described above.

Eligible caregivers will be required to provide written informed consent to the CI. Upon obtaining written informed consent, the CI will send an enrollment SMS to the RapidSMS server, a free and open-source platform. The enrollment SMS is structured and requires the CI to enter the study identification number, the phone number that can be used to receive text message reminders, the child’s date of birth, the preferred language to receive reminders, the child’s first and last name, and the study arm. If the CI sends an incorrectly formatted SMS, he or she will receive an error SMS, which asks the CI to correct the SMS. The RapidSMS server will then send a personalized text message to the newly enrolled caregiver that welcomes him or her to the study (Table 1). The CI will confirm receipt of the enrollment SMS.

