## Discussion

### Differences Between Previous Studies

This proposed study differs from our previous cluster RCT, the M-SIMU study, in several ways [15,19]. First, M-SIMU enrolled infants younger than 5 weeks and provided reminders and incentives for the pentavalent vaccine series at 6, 10, and 14 weeks of age and for measles vaccine at 9 months of age. The significant effect of incentives on measles coverage may be due to caregivers previously receiving travel subsidies and reminders for the 3 pentavalent doses. Contrastingly, the M-SIMI study seeks to enroll caregivers of children aged 6 to 8 months and to provide reminders and unconditional travel subsidies only for measles vaccination.

A second difference, and perhaps a more important one, is that M-SIMU provided conditional incentives for vaccination, where the incentive was only given if the caregiver brought their child for vaccination within 2 weeks of the EPI due date. M-SIMU–employed health facility recorders were stationed at each clinic to confirm a timely vaccination. With busy clinic workers, this conditional approach is difficult to scale because it requires staff at the clinic to document immunization and to calculate whether the immunization was received in time. To counter these logistical and implementation challenges, the M-SIMI trial will provide an incentive unconditionally, that is, the caregiver receives an incentive 3 days before the child’s 9-month birthday and independent of whether the child has been vaccinated for measles.

A third difference between M-SIMU and M-SIMI is in the enrollment strategy. Where the M-SIMU trial employed KEMRI HDSS village reporters to identify births and deaths, this proposed study seeks to leverage CHWs, a component of Kenya’s national community health strategy, to identify and enroll children into a travel subsidy scheme. Village reporters are a unique component of the HDSS, making the external generalizability of our results somewhat limited, whereas numerous countries have national CHWs.

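### The CHW case-finding analysis takes the rival HDSS listing as error-free and plans a specificity with no defined non-eligible pool, so CHWs can be shown equal to HDSS but never better

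*Protocol article*

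**What the plan says.** Protocol article, Data Analysis: "we will conduct a sensitivity and specificity analysis of our CHW approach to identify age-eligible children". The reference is fixed in the next sentence: "The HDSS database, which relies on village reporters to enumerate the population, will be used as the gold standard". The same paragraph then sets the two methods against each other on cost: "We will compare the costs of a CHW versus HDSS approach of identifying eligible children".

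The Enrollment section describes what a CHW reports: "The CHWs will call the field supervisor to notify the study team that they have identified a child aged 6 to 8 months". It describes no report of a child who is not age-eligible. A CI then visits and screens the caregiver. Age 6 to 8 months is an inclusion criterion (Textbox 1), and the child's date of birth is part of the enrollment SMS sent after consent.

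Data Collection plans the link between the sources: "Linkages with HDSS data will be made so that the CHW enrollment approach can be compared with existing HDSS population estimates". Differences Between Previous Studies presents CHWs as the replacement for the earlier method: "Where the M-SIMU trial employed KEMRI HDSS village reporters to identify births and deaths, this proposed study seeks to leverage CHWs". It adds that the CHW route is the more generalizable of the two.

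**The concern.** There are two separate problems.

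**Specificity.** It needs a count of non-eligible persons who were correctly not reported. CHWs send in positives only, so that count must come from HDSS. The article does not say whether the pool is other infants, under-fives or all residents. The wider the pool, the closer specificity comes to 100%, whatever the CHWs do.

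**Reference standard.** HDSS is both the yardstick and one of the two methods being compared. Any eligible child HDSS has missed and a CHW has found is scored as a CHW error, even where the trial's own interviewer has screened that child as 6 to 8 months old and recorded a date of birth. HDSS cannot be found incomplete, because its sensitivity is 100% by definition.

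The article offers CHW enrollment as the more generalizable route. A programme choosing an identification method could be reassured by an uninformative specificity, and could be told that correct extra finds are mistakes.

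**Working it through.** **The plan's own figures.** The CHW analysis has none. The only related calculation is the trial sample size: "Assuming a 70% outcome in the control group, an absolute 15% difference in the primary outcome between control and intervention arms", with "a type 1 error (alpha) of .05 and a power (1-beta) of 0.80". A two-sided test of two proportions gives 121 per arm, or 134 with continuity correction, as stated. Then 134/0.75 = 178.7, rounded up to 179, and 3 × 179 = 537. This reproduces and does not depend on the point made here.

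The documents give no CHW or HDSS counts, so **every count below is an assumption**.

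**Step 1: specificity follows the pool.** Assume HDSS lists 600 eligible children, and CHWs report 500, of whom 400 match HDSS and 100 do not.

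- Sensitivity = 400/600 = 66.7%.
- Positive predictive value (PPV) against HDSS = 400/500 = 80%.
- Specificity = 1 − 100/N, where N is the non-eligible pool, taken to include the 100 non-matches:

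| Pool | N | Specificity |
|---|---|---|
| Other infants | 1,800 | 94.4% |
| Other under-fives | 11,400 | 99.1% |
| All other residents | 80,000 | 99.9% |

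The CHW data are the same in all three rows. With 20 false reports instead, specificity is 90.0% for N = 200, 98.0% for N = 1,000 and 99.9% for N = 20,000.

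**Step 2: perfect CHWs against an incomplete HDSS.** Assume 200 truly eligible children, and CHWs who find all 200 and report nobody wrongly. D is the number of truly non-eligible persons. HDSS lists a fraction H of the eligible children.

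- True positives = 200H; false negatives = 0; false positives = 200(1 − H); true negatives = D.

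| H | CHW sensitivity | PPV | Specificity, D = 200 | Specificity, D = 20,000 |
|---|---|---|---|---|
| 100% | 100% | 100% | 100% | 100% |
| 90% | 180/180 = 100% | 180/200 = 90% | 200/220 = 90.9% | 20,000/20,020 = 99.9% |
| 80% | 160/160 = 100% | 160/200 = 80% | 200/240 = 83.3% | 20,000/20,040 = 99.8% |

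The best attainable score is 100%/100%, which means full agreement with HDSS. Finding more real children than HDSS lowers PPV and specificity. CHW sensitivity does not fall, because an unlisted child drops out of both its numerator and its denominator. HDSS, whose true sensitivity in the lower rows is 90% or 80%, is credited with 100%.

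**Step 3: effect of using the CI check.** Return to Step 1 and assume the CI confirms the age of 50 of the 100 non-matches.

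- Union of HDSS-listed and CI-confirmed = 600 + 50 = 650.
- CHW PPV = 450/500 = 90%, instead of 80%.
- HDSS sensitivity = 600/650 = 92.3%, instead of the assumed 100%.
- CHW sensitivity = 450/650 = 69.2%, instead of 66.7%.

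The main correction falls on PPV and on HDSS; CHW sensitivity moves little.

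**The case against.** Validating a new case-finding route against an existing population register is common practice, and the article states no aim or test of CHW superiority. Its argument for CHWs is generalizability, not better accuracy. True negatives could be had: Setting and Participants says CHWs visit every household at least monthly, so a visit without a call is an implicit negative, and the HDSS linkage can list children outside the age range. Choosing the pool is a definition that a condensed article may leave to a fuller document. The two faults also partly offset: with a wide pool, HDSS omissions barely move specificity, and PPV is not a planned measure. Nothing in the article indicates that HDSS undercounts.

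Much of this stands, and it rules out several stronger readings:

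- A reader might infer that specificity can never be meaningful here. With a pre-specified, narrow pool it could be.
- A reader might infer that CHWs cannot be shown equal to HDSS. They can, at 100%/100%.
- A reader might infer that HDSS omissions are charged against CHW sensitivity. They are not; they enter PPV and specificity.
- A reader might infer that the cost comparison is tilted toward HDSS. The article does not say that costs are divided by HDSS-confirmed children.
- A reader might infer that a date of birth exists for every child called in. The article describes it only for those enrolled.

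What the objection does not remove is the gold-standard rule. That is a stated choice, not an omitted detail, and it contradicts the trial's own screening data for any enrolled child HDSS does not list.

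**Conclusion.** The point holds in limited form. Treating HDSS as error-free scores any CI-confirmed child absent from HDSS as a CHW false positive, gives HDSS 100% sensitivity by assumption, and rules out a finding that CHWs do better. Specificity as planned has no named non-eligible pool and approaches 100% as the pool widens.

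The size cannot be taken from the documents. Under the assumed counts, specificity runs from 94.4% to 99.9% on identical CHW data. An HDSS that lists 90% of eligible children would reduce the PPV of flawless CHWs to 90%. If HDSS is in fact complete, the reference-standard problem has no numerical effect and only the specificity problem remains.

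This is an ancillary analysis, not listed among the Outcomes. It does not touch randomisation, the primary outcome, the sample size or any comparison between arms.

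**What to change.** - Call HDSS a comparator rather than the gold standard. Count CI-confirmed children, at minimum all enrolled children, as truly eligible even if HDSS does not list them.
- Report the sensitivity of CHW and of HDSS, each against the union of HDSS-listed and CI-confirmed children. State that the union misses children whom neither source found.
- Replace specificity with PPV: the share of CHW-reported children confirmed as 6 to 8 months old at CI screening.

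The cost is mostly wording, since CI screening and the HDSS linkage are already planned. The one data requirement is to keep the age-screening result for called-in children who are not enrolled. Among enrolled children alone PPV is 100% by construction, because the age range is an inclusion criterion. If those results were not kept, PPV can cover only children with a recorded screening result, and the report should say so.
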